#### Explorative, secondary other outcomes:

- The Hospital Anxiety and Depression rating scale (HADS) to assess self-reported affective symptoms. It is a 14-item scale with depression subscale and anxiety subscale. Score ranges from 0 to 21, with 0 indicating absence of depression or anxiety and 21 indicating the presence of depression or anxiety. It includes a 7-item 4-point Likert 'depressive symptoms' subscale (0-21) and 7-item 4-point Likert 'Anxiety' subscale (0-21). Both apply a 4 week time interval
- The Short Form Health Survey-36 (SF-36) to assess physical and mental functioning. The SF-36 is widely used a generic measure of health-related quality of life and constitutes well characterised psychometric properties.
- Physical activity recorded over 7 consecutive days by three-axis wrist worn accelerometers (GT9X-BT, Actigraph) will be used to define number of steps and percentage in level of activity (sedentary, light, moderate, vigorous) will be used as measure of physical activity.
- Adverse events classified as serious (led to death, life-threatening, required hospitalization, prolonged hospitalization, led to prolonged or significant disability).

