- Pressure pain thresholds (PPT; increase of >15% is clinically important), defined as the point of minimum pressure that induces an unpleasant sensation is assessed with a digital pressure algometer (Wagner instruments), randomly applied at the painful and two remote locations. The painful level is the trapezius muscle in neck pain patients and at L3 lumbar paravertebral muscles in low back pain patients. Remote sites are the web between the thumb and the index and the proximal one third of the calf. The threshold is determined as the mean of two consecutive measurements, with 30 s in between.

Explorative, secondary sleep-related outcomes:

- The Pittsburgh Sleep Quality Index (cut-off = 6/21; 3 points difference as clinically important) to assess self-reported perceived sleep quality. It is a 19 item scale with 1 week time interval. Its score ranges between 0 and 21 and 0 indicates no sleep difficulty and 21 indicating severe sleep difficulties.
- The Insomnia Severity Index (cut-off = 14/28; 6 points difference as clinically important) to assess self-reported insomnia severity. It is a 5-item 5-point Likert scale applying a 2 week time interval. Its scores range between 0 and 28 and 0 indicates no clinically significant insomnia and 28 indicating severe clinical insomnia.
- Dysfunctional Beliefs and Attitudes about Sleep questionnaire to assess self-reported dysfunctional beliefs and attitudes about sleep. It is a 16-item 5-point Likert scale with scores ranging between 0 and 10. Scores over 4 indicate unrealistic expectations for sleep or unrealistic thoughts about sleep.
- The Epworth Sleepiness Scale to assess self-reported sleep propensity. It is an 8-item 4-point Likert scale, with scores ranging between 0 and 24 and with 0 indicating normal daytime sleepiness and 24 indicating severe excessive daytime sleepiness.
- The Brugmann Fatigue Scale to assess self-reported fatigue severity with mental fatigue subscale and physical fatigue subscale. The score ranges from 0 to 24 and higher scores indicate a higher subjective level of fatigue.

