From the sleep diary, sleep efficiency was computed as the ratio of total sleeping time to the total time spent in bed, serving as an indicator for sleep restriction therapy. Sleep efficiency represents a possible mismatch between time spent in bed and total sleep time. This therapy involves limiting the hours spent in bed as closely as possible to the actual hours of sleep (i.e. determining the sleep window). To achieve this, the time in bed was restricted to the mean sleep time of the previous week, as recorded in the sleep diary, which heightened sleep pressure. Consequently, excessive time in bed was addressed, and a mild form of sleep deprivation ensued. Importantly, the sleep window was never reduced below 5 hours per night, and the participant was not allowed to make any changes without consulting the therapist. In the long term, this approach facilitates faster sleep onset, improves sleep continuity, and results in a deeper, higher-quality sleep by stabilizing the circadian rhythm and balancing the production of melatonin and cortisol. Daytime naps were permitted, but their duration was restricted to a maximum of 15 minutes and only allowed if taken before 2 p.m.

Changes in the prescribed, restricted time in bed occurred using the following guidelines:

- Sleep efficiency = 80-85% : sleep window is retained
- Sleep efficiency < 80% : a new sleep window is determined by making the total time in bed equal to the mean total sleep time of the past week (sleep window  $\geq$  5 hours because of safety and health concerns)
- Sleep efficiency > 85% : sleep window is extended by 15 minutes

Together with an efficacy > 85% any use of sleep-related medication was phased out in agreement with the participant and in close collaboration with the general practitioner of the participant.

For participants with high levels of anxiety, an exception was permitted. This allowed them to choose their bedtime freely one night per week to avoid heightened alertness caused by stress arising from sleep restriction therapy.

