Descriptive statistics were used to report the demographic variables and baseline characteristics of the participating nCSP patients per intervention group, with means (Standard Deviation [SD], range and Inter Quartile Range [IQR]) for continuous variables and frequency (%) for categorical variables. All analyses were by intention-to-treat, with all participants included in the analysis according to their randomly allocated treatment. All analyses were performed in SPSS 24.0. For average pain intensity (primary outcome) and for all explorative, secondary outcomes, the change between baseline and other time points was calculated:  $\Delta 1 = \text{baseline (T0)} - \text{post-treatment (T1)}$ ;  $\Delta 2 = \text{T0} - \text{3-month follow-up (T2)}$ ;  $\Delta 3 = \text{T0} - \text{6-month follow-up (T3)}$ ; and  $\Delta 4 = \text{T0} - \text{12-month follow-up (T4)}$ . Differences in the change in average pain intensity at 12-month follow-up (primary outcome at primary endpoint) and at the other time points (immediately post-intervention, and at 3- and 6-month follow-up) were analysed using a random-intercept fixed slope linear mixed model (incl. LSD post-hoc analyses), which was applied using an unstructured covariance matrix. Linear mixed models are a likelihood-based estimation procedure whereby likely values for missing data are estimated from information contained in the observed data, resulting in non-biased estimates providing data are missing at random. The model included treatment, time, and treatment\*time as fixed effects together with a random intercept for each patient. Model assumptions were evaluated visually using residual plots. Mean group differences (95% confidence interval) at the different time points and their p-values and effect sizes for the intervention comparisons are reported. Level of significance for the primary outcome was set at  $\alpha .05$ . Effect sizes were calculated as Cohen's d (interpreted as  $>1.3$  = very large;  $.80-1.29$  = large,  $.50-.79$  = medium,  $.20-.49$  = small,  $<.20$

= negligible). The same analysis was used to evaluate the explorative, secondary outcomes at the different time points.

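### Only serious adverse events are an outcome, so non-serious harms are not counted as events, and the planned mixed model does not fit event data

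*Combined protocol and SAP*

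**What the plan says.** Under Explorative, secondary other outcomes, the single harms outcome is "Adverse events classified as serious (led to death, life-threatening, required hospitalization, prolonged hospitalization, led to prolonged or significant disability". The document names no non-serious event outcome, no method or window for collecting events, no assessment of relatedness and no event table.

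The CBTi content (part ii, Behavioral therapy) describes two exposures that appear only in the experimental arm:

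- Time-in-bed restriction: "Consequently, excessive time in bed was addressed, and a mild form of sleep deprivation ensued". The sleep window has a floor of "5 hours because of safety and health concerns".
- Sleep medication: once sleep efficiency exceeds 85%, "any use of sleep-related medication was phased out in agreement with the participant", together with the general practitioner.

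The Interventions section gives 15 sessions of cognition-targeted exercise in BEPM-only and 9 in CBTi-BEPM. That exercise is to be performed to a set count whatever the pain.

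The plan also measures related symptoms in both arms. These include the Epworth scale ("to assess self-reported sleep propensity"), the Brugmann scale ("to assess self-reported fatigue severity with mental fatigue subscale and physical fatigue subscale"), the HADS ("to assess self-reported affective symptoms"), the Insomnia Severity Index, the Pittsburgh index and the BPI pain items. The Design section places assessments at baseline, post-intervention, and 3, 6 and 12 months.

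Item 7 of the Statistical analysis plan computes change from baseline, fits a linear mixed model, and then states: "The same analysis was used to evaluate the explorative, secondary outcomes at the different time points".

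**The concern.** By its own account the plan exposes one arm to some sleep deprivation and to a medication phase-out, and it gives the other arm six more exercise sessions (15 − 9 = 6). Non-serious harms could therefore differ between arms in either direction. A definition tied to death, threat to life, hospitalisation and lasting disability would not register most of them.

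Two consequences follow. First, a harms table restricted to serious events may well be nearly empty, and it would say nothing about tolerability. Second, the SAP leaves this outcome without a usable analysis: a change score needs a baseline value, and an adverse event has none.

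**Working it through.** **Inputs.** The total sample is 120, allocated 1:1, so 120/2 = 60 per arm. With the planned 20% loss, 60 × 0.80 = 48 per arm. The documents give no event rates, so every rate below is an assumption. The plan states no harms figure to reproduce, and the sample size of 120 is not disputed here.

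**Timing of the existing measures.**

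- Table 4 puts the CBTi sessions in weeks 3, 4, 5, 6, 8 and 10. The sleep diary runs through the whole intervention, so restriction may continue after week 10.
- The first outcome assessment after baseline is post-intervention, that is, after week 14.
- Stated recall periods are 1 week (Pittsburgh), 2 weeks (Insomnia Severity Index) and 4 weeks (HADS); the BPI intensity items cover 24 hours or the present moment. The longest reaches back to 14 − 4 = the end of week 10 at the earliest. No recall period is stated for the Epworth or Brugmann scales.
- The sleep diary records sleepiness and fatigue during treatment, but it is described only for the CBTi arm and as a therapy tool.

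No outcome is therefore scheduled in the weeks when restriction begins. The scales yield mean scores, not counts of events.

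**What serious events alone can show.** With zero events in n patients, the one-sided 95% upper limit is 1 − 0.05^(1/n) and the upper limit of a two-sided interval is 1 − 0.025^(1/n).

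- n = 60: 4.9% and 6.0%.
- n = 48: 6.1% and 7.4%.
- At an assumed true risk of 1%, the chance of at least one event in an arm of 60 is 1 − 0.99^60 = 45%; over both arms it is 1 − 0.99^120 = 70%.
- Power for an assumed 1% versus 5%, 60 per arm: 25% by normal approximation, 5% by Fisher's exact test.

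**What counting all events would add.** Power at two-sided 5% with 60 per arm:

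| Assumed rates | Normal approximation | Fisher exact |
|---|---|---|
| 10% vs 20% | 33% | 25% |
| 10% vs 30% | 79% | 73% |
| 20% vs 40% | 67% | 60% |
| 20% vs 45% | 84% | 79% |

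From 10%, the rate detectable with 80% power (normal approximation) is 30.4% with 60 per arm and 33.3% with 48.

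As a guide to precision, the approximate half-width of a 95% interval for a risk difference is 1.96 × √[p1(1 − p1)/60 + p2(1 − p2)/60]. For 10% versus 30% it is 1.96 × √(0.0015 + 0.0035) = 14 percentage points. For 10% in both arms it is 1.96 × √(0.0015 + 0.0015) = 11 points.

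**What the scales can show.** The standardised difference detectable with 80% power is (1.960 + 0.842) × √(2/n): 0.51 for n = 60 and 0.57 for n = 48, from post-intervention onward.

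**The case against.** The strongest reply is that the plan does measure the relevant symptoms. Sleepiness, fatigue, insomnia, sleep quality, mood and pain, along with polysomnography and the SF-36, are all compared between randomised arms. This stands. A reader might infer that non-serious harms go wholly unmeasured, or that the trial cannot compare safety at all; the documents support neither. What remains is that these are mean scores taken after treatment ends, so transient effects and discrete events are missed.

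Second, low precision comes from about 60 patients per arm, and the fix does not cure it. This also stands. The 4.9%, 6.0% and 45% figures describe rare serious events, not the missing non-serious ones, for which no rate is available.

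Third, the outcome line could mean that all events are recorded and then classified by seriousness. That is possible, but nothing in the document says so, and the mixed-model problem remains under either reading.

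Fourth, the objectives concern effectiveness and no safety conclusion is planned. It is therefore conjecture that an empty table would be presented as proof of safety. Adverse events are nevertheless a listed outcome and need a workable definition and analysis.

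Fifth, the document does not name falls, accidents or withdrawal symptoms as expected harms, and the medication phase-out is conditional. The point therefore rests only on the exposures the plan itself describes.

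Finally, having therapists ask about pain flares at each session would conflict with the therapy concept, which directs attention away from pain. It would also invite uneven recording, because therapists know the arm they deliver. This is accepted and shapes the fix.

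**Conclusion.** The point holds in a limited form. The only adverse-event outcome is serious events, without a stated collection method or window. Non-serious harms are visible only through scale means, none taken within the 14 treatment weeks. The blanket mixed model cannot be applied to adverse events.

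On size, zero serious events in an arm would leave a true risk of up to 4.9% (60 analysed) or 6.1% (48 analysed) open, one-sided 95%. Counting all events would reveal only large differences, roughly 10% versus 30%, so the gain is description and estimation, not a test of equal safety. These detectable differences rest on assumed event rates.

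The primary pain comparison is unaffected. Nothing here shows that either arm is unsafe, and the documents do not support that inference. This is an inexpensive improvement that changes what the trial can say about harms.

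**What to change.** 1. Define the outcome as all adverse events, each classified as serious (by the criteria already listed) or non-serious.
2. Collect them in both arms with one identical, neutrally worded, patient-reported item, stating the period it covers. Use existing contacts: the online alliance questionnaires after weeks 2 and 8, and the post-intervention, 3-, 6- and 12-month assessments. The alliance questionnaires are declared not to be trial outcomes, so this item must be designated as one. Do not add therapist-led pain-flare prompts at each session.
3. In item 7 of the SAP, exempt this outcome from the change-score mixed model. Report the number of patients with at least one event and the number of events by arm, with an exact 95% interval for the risk difference. Make no claim of equal safety.
4. Parts of the document are in the past tense. If collection is already complete, apply the count analysis and limit harms conclusions to serious events.

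The cost is a small extra questionnaire burden, one table and some recall error. Only the week 8 contact falls within the CBTi weeks. An item there would look back over weeks 3 to 8, which hold five of the six CBTi sessions; the post-intervention item would have to cover weeks 9 to 14. No extra staff or procedure is needed, and the sample size does not change.

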#### **Interventions:**

Both groups receive 18 sessions of approx. 30 minutes over 14 weeks. All sessions are delivered by physical therapists (Master of Science), and are one-on-one, individualized sessions (except for one group pain educational session of 1h) using principles of person-centred care and applying guidance towards self-management. The experimental intervention comprises 6 sessions of CBTi, integrated in 12 sessions of BEPM (i.e., CBTi-BEPM). The control intervention comprises of 18 sessions of BEPM (BEPM-only). The treatment contrast lies therefore in the 6 CBTi sessions. CBTi includes sleep education, self-monitoring of sleep patterns, time-in-bed restriction, stimulus control, sleep hygiene, cognitive restructuring, and relaxation. For details, see. BEPM includes pain neuroscience education (PNE; 3 sessions) and cognition-targeted exercise therapy. In CBTi-BEPM 9 sessions of cognition-targeted exercise therapy are provided, while in the BEPM-only intervention 15 sessions of cognition-targeted exercise therapy are provided to ensure balanced treatment arms regarding therapy/therapist exposure time. For full details on BEPM, see.

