**Sample size calculation:**

Sample size (n=120) is calculated using G\*Power based on the effects on pain in a pilot study (Cohen's  $f = 0.25$ ,  $\alpha = .05$ ,  $\text{power} = .80$ ), accounted for F-tests and 20% loss to follow-up after one year.

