**Randomisation:**

Randomization is computer-generated at the Biostatistics Unit of Ghent University by an independent investigator, uninvolved in any other trial aspects. Block randomisation was used (ratio 1:1) for the two treatment centres (Ghent; Brussels) separately, with stratification for sex (male; female) and dominant pain location (neck; low back). The randomisation is performed by an independent researcher, who places papers indicating group assignment in sequentially numbered, opaque, and sealed envelopes. Concealed allocation is ensured since the independent researcher – who will be the only person with access to the envelopes – writes the initials of the selected participants on the appropriate envelope before opening them.

**Outcome measures:**Primary outcome:

The primary clinical outcome is defined as average pain intensity, assessed using the Brief Pain Inventory (BPI) item 'average pain intensity in the last 24h' evaluated on an 11-point NRS (30% decrease is clinically important).

Explorative, secondary pain-related outcomes:

- BPI worst pain intensity (last 24h) on an 11-point (0–10) numeric rating scale
- BPI least pain intensity (last 24h) on an 11-point (0–10) numeric rating scale
- BPI pain intensity now on an 11-point (0–10) numeric rating scale
- BPI pain severity: the mean of the four pain intensity items
- BPI pain interference: the BPI also evaluates the pain interference related to general activity, walking, work, mood, enjoyment of life, relation with others and sleep on separate 11-point numeric rating scales.
- The Central Sensitisation Inventory (CSI; cut-off value of 40/100 to indicate the presence of central sensitization-related symptoms) to assess symptoms of central sensitisation. The CSI uses 25 statements related to current health symptoms, indicative of central sensitization (scored on a five-point Likert scale ranging from zero to four).

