| Week 10 | CTET (face-to-face, 30 minutes)                                                                                                               |                                 |

|                                            |                                 |
|--------------------------------------------|---------------------------------|
| Week 11                                    | CTET (face-to-face, 30 minutes) |
| Week 12                                    | CTET (face-to-face, 30 minutes) |
| Week 13                                    | CTET (face-to-face, 30 minutes) |
| Week 14                                    | CTET (face-to-face, 30 minutes) |
| CTET = Cognition-Targeted Exercise Therapy |                                 |

Table 2. Organization of the therapeutic sessions

Therapeutic alliance between the therapist and patient was checked twice during the intervention, using an online questionnaire. This questionnaire was filled out by both the therapist and the patient after week 2 and week 8 of the intervention. It is important to note that the results of this questionnaire were not considered as trial outcomes. Instead, they served solely as a feedback tool, enabling therapists to address any issues in the therapeutic alliance as they arose.

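### Patients have 16 individual therapist sessions each, but no analysis allows for therapist; the effect on the 12-month contrast depends on whether therapists treat one arm or both, which is not stated

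*Combined protocol and SAP*

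**What the plan says.** The Interventions section says of both arms: "All sessions are delivered by physical therapists (Master of Science"). Tables 2 and 4 fix the number of contacts. The control arm has 15 exercise sessions and one individual pain education session. The experimental arm has 9 exercise sessions, 6 CBTi sessions and the same individual education session. Each arm also has one group education session and one online session.

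Item 7 of the statistical analysis plan fits treatment, time and their interaction "as fixed effects together with a random intercept for each patient". The covariance is described as one "which was applied using an unstructured covariance matrix". The sensitivity analyses add baseline pain or baseline insomnia severity and nothing else.

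The Randomisation section says "Block randomisation was used (ratio 1:1) for the two treatment centres (Ghent; Brussels) separately", with sex and pain location as strata; therapist is not a stratum. The sample size is "accounted for F-tests and 20% loss to follow-up after one year", with no allowance for clustering. The number of therapists, patients per therapist, and whether a therapist works in one arm or both are not stated.

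**The concern.** The protocol itself makes therapist differences plausible. Therapists choose the exercises, communication is treated as central to the exercise therapy, and CBTi is shaped to the individual. Alliance was also monitored: "Therapeutic alliance between the therapist and patient was checked twice during the intervention".

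If therapists do affect 12-month pain, patients of the same therapist are correlated. A patient intercept, and any covariance among one patient's repeated measures, describes correlation within a patient and cannot carry correlation between patients.

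The stake is the primary test. If each therapist works in one arm only, the reported interval is too narrow, and a difference between two sets of therapists could be read as an effect of CBTi. A reader cannot tell from the plan whether this applies.

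**Working it through.** **Session count.** Control: 15 + 1 = 16 individual face-to-face sessions. Experimental: 9 + 6 + 1 = 16. Adding one group and one online session gives the stated 18.

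**The plan's own figure.** "Sample size (n=120) is calculated using" G*Power with f = 0.25, α = .05, power .80 and 20% loss. A two-group between-subjects test in a repeated-measures ANOVA, assuming 2 measurements correlated at .5, needs 98; 98/0.8 = 122.5, so 123. Assuming 3 measurements correlated at .6, it needs 96, and 96/0.8 = 120. The stated 120 is therefore reproducible only under settings the plan does not give. Neither route contains a clustering term. After 20% loss, 120 × 0.8 = 96, or 48 per arm.

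**Assumed, because the documents give no figures:** k therapists per arm from 3 to 12; ICC from .01 to .05; equal caseloads.

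**Case 1: therapists nested in arm.** With m = 48/k patients per therapist, the true variance of the arm difference is DE = 1 + (m − 1) × ICC times the variance that assumes independence. The actual type I error is 2[1 − Φ(1.96/√DE)]. For k = 4 and ICC .05: m = 12; DE = 1 + 11 × .05 = 1.55; the standard error should be √1.55 = 1.245 times larger; type I error is 2[1 − Φ(1.574)] = 11.5%. Each cell below gives DE and type I error.

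| Therapists per arm | m | ICC .01 | ICC .03 | ICC .05 |
|---|---|---|---|---|
| 3 | 16 | 1.15, 6.8% | 1.45, 10.4% | 1.75, 13.8% |
| 4 | 12 | 1.11, 6.3% | 1.33, 8.9% | 1.55, 11.5% |
| 6 | 8 | 1.07, 5.8% | 1.21, 7.5% | 1.35, 9.2% |
| 8 | 6 | 1.05, 5.6% | 1.15, 6.8% | 1.25, 8.0% |
| 12 | 4 | 1.03, 5.3% | 1.09, 6.0% | 1.15, 6.8% |

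Simulation (20,000 trials per cell, no true effect, two-sample comparison at 12 months rather than the full mixed model) agrees to within about half a percentage point. In the same runs a t-test on therapist means held about 5%.

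**Case 2: therapists treat both arms, same relative effect.**
- If therapists are balanced across arms, the therapist effect cancels from the contrast. The ratio of true to assumed variance is 1 − ICC. At ICC .01, .05 and .10 the standard-error ratio is √.99 = .995, √.95 = .975 and √.90 = .949, and type I error is 4.9%, 4.4% and 3.9%.
- If patients are assigned to therapists independently of arm, patients are exchangeable between arms when there is no effect, so the test keeps its level. Simulated rejection was 4.7-5.3% for 4, 6 or 8 therapists and ICC .01-.10.

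**Case 3: therapists treat both arms but differ in relative effect.** Assume therapist and therapist-by-arm variance shares of .02 each, balanced caseloads, and m patients per therapist in each arm. The variance ratio is (1 − .04) + m × .02.
- 4 therapists, m = 12: .96 + .24 = 1.20, type I error 7.4% (simulated about 7.5%).
- 8 therapists, m = 6: .96 + .12 = 1.08, type I error 5.9% (simulated about 6%).

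**The case against.** A reader might infer that the standard error is wrong whenever therapists differ, or that the model is right only if they do not differ at all. Neither holds. Under case 2 the test is valid or mildly conservative whatever the ICC.

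A reader might also infer that each therapist worked in one arm. The documents neither say this nor rule it out, so an inflated error rate has not been shown to occur. Nor does each patient have 18 individual therapist-delivered sessions: one is a group session and one is a web slideshow.

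The other side can add that every ICC and therapist number is assumed, and that with 12 therapists per arm the nested inflation is small (about 5-7%). It can also say that the plan contains standardising features: a template for the individual education session, shared education and exercise content across arms, and an alliance questionnaire used as feedback so that therapists could correct problems. Fuller intervention details are in cited sources not available here.

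All of this stands, and it limits the claim. It does not remove the gap. Freedom over exercise choice works against standardisation, the arrangement of therapists is undisclosed, and no planned analysis would reveal a therapist effect if one existed.

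**Conclusion.** The point holds in conditional form. The plan omits a design fact on which the validity of the primary interval depends, and it has no analysis that allows for therapist. The text establishes the missing therapist term and the missing description; the figures rest on assumed therapist numbers, ICCs and equal caseloads, with 48 analysed per arm.

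- Nested in arm: type I error about 5-7%, 7-11% and 8-14% at ICC .01, .03 and .05 for 8 down to 3 therapists per arm; about 5-7% over the same ICCs with 12 per arm.
- Both arms, no therapist-by-arm effect: about 5% if assignment to therapist is independent of arm, about 4-5% if therapists are balanced across arms.
- Both arms, variance shares of .02 and .02: about 6-7.5% for 8 down to 4 therapists.

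This justifies disclosure and a sensitivity analysis. It does not justify calling the primary analysis wrong.

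**What to change.** Record the treating therapist for each patient, and state how many therapists there are and whether each treats one arm or both. Keep the primary model. Pre-specify one sensitivity analysis of the 12-month contrast with Satterthwaite degrees of freedom:

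- if therapists are nested in arm, add a therapist random intercept, or compare therapist means;
- if they treat both arms, add a therapist random intercept and a therapist-by-arm random effect, since an intercept alone misses case 3.

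Report the number of therapists, patients per therapist by arm, and the estimated ICC. Qualify the conclusion if the sensitivity 95% interval changes whether zero is excluded.

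The cost is one variable and one extra model. The therapist-patient link should be recoverable, because both parties completed the alliance questionnaire. The drawback is a wide interval when therapists are few: with 3 per arm, a comparison of therapist means has 3 + 3 − 2 = 4 degrees of freedom. In the nested case the analysis corrects the interval but cannot fully separate therapist from treatment, which is why it is proposed as a sensitivity analysis and not as a new primary model.
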